### Sample Size Calculation

On the basis of what was proposed for the design of the RCTs [27], the number of participants will be calculated. Taking 2 RCTs that aimed to increase physical activity levels through walking [18,19] as reference, the sample will be calculated considering an absolute difference of 3% (α error of .05 and statistical power of .80) between the intervention group and the control group in the mean percentage of cardiorespiratory endurance (SD 5), giving a required sample of 99 participants for each group (intervention and control).

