### Statistical Analysis

The normality of the data will be checked through the Kolmogorov-Smirnov test, which will indicate the steps to be taken in relation to the comparison tests. Once the pretest tests have been performed, comparison analyses will be performed between groups (2-tailed Student *t* test or Mann-Whitney *U* test) to check the homogeneity of the groups. At the conclusion of the final evaluations of the study, intragroup differences will be analyzed using a statistical test of repeated measures (Student *t* test for related samples or Wilcoxon signed-rank test), along with the intergroup differences (Student *t* test or Mann-Whitney *U* test).

Cohen *d* will be used to determine the effect size on variables in which significant differences are found, using the following scale: 0.2 or greater=small, 0.5 or greater=moderate, and 0.8 or greater=large [33]. In addition, regression analyses will be performed incorporating the covariates. The simple imputation method will be used for all analyses [34], keeping the participants in the group to which they were assigned (intervention or control) regardless of the sessions they attended [35]. In valid cases, analyses will be performed to determine sensitivity [36]. For all tests, statistical significance will be set to *P*<.05. The data will be analyzed using SPSS statistics (version 29; IBM Corp).

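### Single imputation is fixed for all analyses with nothing to carry its uncertainty; if final values are missing, the main P values, estimates and Cohen d are distorted

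*Protocol article*

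**What the plan says.** The Statistical Analysis section commits to one way of handling missing data: "The simple imputation method will be used for all analyses [34], keeping the participants in the group to which they were assigned". Participants stay in their arm "regardless of the sessions they attended". The tests are Student t or Mann-Whitney between groups, paired t or Wilcoxon within groups, and regressions with the covariates, all judged at P<.05. Cohen d is computed where a difference is significant. The check on the imputation is one sentence: "In valid cases, analyses will be performed to determine sensitivity".

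The section does not say which single-imputation rule will be used. It describes no step that carries the uncertainty of the filled values into the standard errors, such as multiple imputation with pooling or a likelihood-based model. The article gives no expected rate of missing outcomes.

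**The concern.** A value filled once and then analysed as data claims information that the trial did not collect. Two kinds of error follow, depending on the rule.

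- **Fill from the participant's own arm** (arm mean, or a regression prediction within arm). The difference stays about right, but the filled values have too little scatter and the sample size is counted in full. The standard error is too small and false positives rise. Cohen d is inflated too, because it divides by the shrunken SD and is computed only for significant results.
- **Fill that ignores the arm's final level** (overall mean, or the baseline value). Filled participants show no treatment difference, so the estimated effect is pulled toward zero.

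Missing finals are a realistic prospect. The programme lasts a semester, the Ethical Considerations section allows withdrawal at any time, and outcomes are assessed only at the beginning and end, so a student who leaves has no later value. The imputed analysis is the one on which the trial's conclusion would rest.

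**Working it through.** **Inputs from the article.** 99 per group and SD 5 (Sample Size Calculation); planning difference 3, from "the sample will be calculated considering an absolute difference of 3" percent; "α error of .05 and statistical power of .80". Two-tailed testing is written for the baseline comparison and is assumed here for the final one.

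**Inputs assumed.** Missing fraction m of 5%, 10%, 20% or 30%, equal in both arms and completely at random; baseline-to-final correlation ρ of 0.5 or 0.8.

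**The plan's own figure.** With difference 3 and SD 5, n per group = 2 × (1.96 + 0.8416)² × 5² / 3² = 43.6, so 44, not 99. That is a separate matter. The calculations below use 99 because it is the planned size.

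**Arm-mean fill.** Let n be the arm size.
- True SE of an arm mean, which rests on n(1−m) values: σ / √[n(1−m)].
- SE the t test reports: the filled values add no scatter, so the variance is about σ²(1−m), divided by the full n, giving σ√[(1−m)/n].
- Ratio of reported to true SE: 1−m.
- Type I error: 2Φ(−1.96(1−m)) = 6.3%, 7.8%, 11.7% and 17.0% at 5%, 10%, 20% and 30% missing.

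**Regression fill by arm.** The same argument gives a variance ratio of [ρ² + (1−ρ²)(1−m)] / [ρ² + (1−ρ²)/(1−m)]. At m = 0.3 and ρ = 0.5 this is 0.775 / 1.321 = 0.587, an SE ratio of 0.766 and a type I error of 2Φ(−1.50), about 13%. At ρ = 0.8 it is 0.892 / 1.154 = 0.773, an SE ratio of 0.879 and about 8.5%.

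**Overall-mean or baseline fill.** A fraction m in each arm contributes no difference, so the expected estimate is (1−m) × 3 = 2.85, 2.70, 2.40 and 2.10.

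**Simulation.** Two-sample t test on the completed data, 10,000 runs under no effect. Ranges run over the two values of ρ; the simulation error of a 5% rate is √(0.05 × 0.95 / 10,000), about 0.2 percentage points.

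| Type I error, % | 5% missing | 10% | 20% | 30% |
|---|---|---|---|---|
| Arm mean | 5.9-6.4 | 7.7 | 11.7-12.2 | 16.8-17.3 |
| Regression by arm | 5.1-5.5 | 5.8-7.5 | 7.6-9.3 | 8.7-14.2 |
| One random regression draw by arm | 5.4-5.6 | 6.0-6.9 | 6.6-9.1 | 8.3-11.8 |
| Overall mean | 4.9-5.1 | 4.9 | 5.1-5.3 | 4.7 |
| Baseline value | 4.6-5.0 | 5.1-5.3 | 4.9-5.1 | 4.8 |
| Observed cases only | 5.0-5.2 | 4.8-4.9 | 5.1-5.4 | 5.0-5.1 |

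With a true difference of 3 (5,000 runs), the average estimate was:

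| Rule | 5% missing | 10% | 20% | 30% |
|---|---|---|---|---|
| Overall mean | 2.85-2.86 | 2.68-2.70 | 2.40-2.41 | 2.08-2.11 |
| Baseline value | 2.84 | 2.70-2.71 | 2.40 | 2.07-2.10 |

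The other methods stayed between 2.98 and 3.02.

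**Unequal dropout under baseline fill.** With 30% missing in one arm, 10% in the other and a common change of 2 in both, the expected bias under no effect is (0.30 − 0.10) × 2 = 0.4 against the arm with more dropout. The simulated bias was 0.40 and the type I error 8.4%.

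**Cohen d.** The planning values give 3/5 = 0.60. Under arm-mean fill at 20% missing, the SD becomes about 5 × √0.8 = 4.47 and d about 3/4.47 = 0.67. Under baseline fill, d is about 2.4/5 = 0.48, which moves the effect from moderate to small on the article's own scale.

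The rank tests, paired tests and covariate regressions were not simulated; the figures apply to the between-group t test.

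**The case against.** The strongest reply is that nothing here is certain to happen. The article gives no attrition rate, and a right to withdraw is not evidence of dropout. With no missing finals the method does nothing, and at 5% missing type I error is 4.6-6.4%. The rule is unnamed, and the largest figures belong to arm-mean fill, which the article does not say it will use. Overall-mean or baseline fill, with equal random missingness, errs toward no effect. All of this stands, and it limits the claim.

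A reader might therefore infer too much in three ways.
- That the P values will be wrong whatever happens, or that false positives must rise. The document does not support this: both the occurrence and the direction depend on facts it does not state.
- That confidence intervals will be wrong. The Statistical Analysis section mentions none. The planned outputs at risk are P values, estimated differences and Cohen d.
- That stopping the shuttle run early creates a missing value. Under Cardiorespiratory Fitness, stopping ends the test and the minute reached is scored.

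A second reply is that the valid-cases analysis already protects the trial. It helps: under completely random missingness the observed-case t test held type I error at 4.8-5.4%, so a discrepancy would be visible. But it is labelled a sensitivity analysis, and the imputed result remains the main one.

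A third is that the details belong in a fuller document. That would excuse silence on the rule. It does not excuse the choice, which is stated and applied to every analysis. Each variant tested fails in one way or the other, so naming the rule would not be enough.

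**Conclusion.** The point holds in conditional form. The article fixes single imputation for all analyses and follows it with tests that treat filled values as observed. If finals are missing, the main result is distorted, and the unnamed rule decides how.

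Fill from the participant's own arm inflates false positives: to about 12% (arm mean) or 8-9% (regression) at 20% missing, and 17% or 9-14% at 30%. Overall-mean or baseline fill loses a share of the effect equal to the missing fraction: 20% of it at 20% missing. Baseline fill can also inflate false positives when dropout is unequal and both arms change.

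This rests on four assumptions: that simple imputation means single imputation, as the wording suggests (the cited source was not consulted); the missing rates, which are not in the article; missingness completely at random, except in the one unequal-dropout case; and correlations of 0.5 to 0.8. At 5% missing or less the matter is minor.

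**What to change.** Keep every participant in the assigned group, but replace single imputation in the main analysis with a method that reflects the missing information. Either of these would do:

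- Multiple imputation by arm, from the baseline outcome and the covariates already collected, pooled by Rubin's rules. Weekly steps can be added where available, but participants submit those files themselves, so drop-outs may lack them.
- A likelihood-based model of the baseline and final values, or a baseline-adjusted regression on the observed finals. With only two assessments, this is the simpler route. It is valid if missingness depends only on arm and the baseline variables in the model, and the model is adequate.

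Keep the valid-cases analysis as sensitivity. A delta-shift analysis, which assumes worse outcomes in drop-outs, is optional. State the choice before final data are seen.

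The cost is a little more analysis work. Relative to mean or regression fill, standard errors become slightly larger, and correct. Recruitment, visits and measurements do not change.

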Given that adults exhibit low compliance with physical activity recommendations, in particular the university population, which is in a period where daily time is prioritized in their academic activities, the performance of a physical activity intervention based on increasing the number of daily steps and monitored through step trackers represents a potential way to overcome the barriers that hinder the practice of physical activity. In addition, given that the use of this technology provides personalized support, it is reasonable to hypothesize that performing a physical activity intervention that increases the number of daily steps could improve some health indicators.

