#### Upper Body Muscle Strength

Using a digital dynamometer (Takei T.KK.5401; Takei Scientific Instruments Co, Ltd), grip strength will be evaluated. For each hand, the average of 2 measurements will be calculated.

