#### Body Composition

Using a digital scale and a stadiometer, weight and height will be measured (Tanita MC-780U [Tanita Corporation] and Seca 222 [Seca, GmbH & Co], respectively). For weight, the participant must be without shoes and with as little clothing as possible, while for height, they must be in a standing position, obtaining the value at the end of a normal inspiration. Both measurements will be taken in duplicate using the average to calculate the BMI.

Waist circumference will be determined as mentioned subsequently. On the right side of the body, a mark will be made on the skin at the height of the last rib, then a mark will be made on the skin at the top of the iliac crest. The distance between both marks will be calculated, and, at the midpoint, a final mark will be made. The same procedure will be performed on the left side. Using a tape measure, which must be at the height of both end marks on each side, the value will be determined at the end of a normal expiration. For the analyses, the average of 2 measurements will be used.

The percentage of adipose and muscle tissue will be calculated from the average of 2 evaluations performed in a state of rest and fasting, with the minimum amount of clothing and after urinating and resting for 15 minutes, using tetrapolar electrical bioimpedance (Tanita MC-780U). It will be complemented by the measurement of skinfolds, body perimeters, and bone diameters [32].

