Regarding the results, cardiorespiratory fitness, muscle strength, and body composition were included because of their value as relevant clinical markers. Current evidence shows that higher fitness levels in youth are associated with better indicators of cardiometabolic health and overall well-being [13,18]. In addition, studies have linked muscle condition with a better perception of health in adolescents [5], which reinforces the relevance of these indicators as outcomes of this study.

Methodologically, the use of a validated wrist device, combined with daily manual logging, addresses both ethical considerations of data privacy and the intention of encouraging self-regulation and awareness of participants’ own physical activity [19]. This component has been described as an effective behavior change strategy in digital interventions [16,18]. Likewise, the risk of reactivity to initial monitoring is recognized [21,38]; therefore, extended duration seeks to minimize this effect and allow a more stable analysis of behavior over time.

The implementation of this study and the subsequent results could be useful for the organizations in charge of providing comprehensive well-being to university students, offering programs that are not only dedicated to their professional training but also contribute to improving their health. This research also aligns with Sustainable Development Goal 3, target 3.4 [39], which aims to promote more active lives and contributes to reducing premature mortality from non-communicable diseases, along with promoting mental health and well-being [37].

The strength of this research is that the intervention will be based on walking, which is an easy and low-cost activity to perform because it does not need additional implements to those used daily by a person nor does it require sports facilities. The device used to track the steps is low cost, so it is accessible to anyone; its use can be constant throughout the day because it does not cause major discomfort when used as a watch that adapts to the characteristics of the wrist, in addition to providing information on physical activity of better quality than that collected through self-reports.

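### Every test is judged at P<.05 with no primary outcome named, although the trial is sized on cardiorespiratory endurance alone, so a claim drawn from the set of outcomes does not carry a 5% error rate

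*Protocol article*

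**What the plan says.** All references are to the protocol article.

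- **Threshold.** Statistical Analysis: "For all tests, statistical significance will be set to" P<.05. The section covers baseline comparisons, within-group pre-post tests in each arm, between-group tests and covariate regressions. It gives no ranking of outcomes and no adjustment. Cohen d is to be calculated only for variables with a significant difference.
- **Sizing.** Sample Size Calculation: "the sample will be calculated considering an absolute difference of 3" percent with SD 5, for cardiorespiratory endurance only, with "α error of .05 and statistical power of .80", giving 99 per group.
- **Outcomes.** Anticipated Findings lists three domains side by side: "cardiorespiratory fitness, muscle strength, and body composition were included because of their value as relevant clinical markers". Grip is recorded separately by side ("For each hand, the average of 2 measurements will be calculated"). The Body Composition section yields BMI, waist circumference, adipose percentage and muscle percentage, and adds an unstated number of skinfolds, perimeters and diameters. No outcome is called primary or secondary.
- **Hypothesis.** The Introduction considers it reasonable to hypothesise that "performing a physical activity intervention that increases the number of daily steps could improve some health indicators".

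**The concern.** The trial is sized as if it had one outcome tested once at .05. The analysis then gives the same .05 to every outcome and every kind of test, and the hypothesis does not say which indicator has to improve. If the report draws its conclusion from whichever comparisons come out significant, the 5% error rate used for sizing does not describe that conclusion.

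Two features add to this. Within-group tests appear alongside the between-group tests with no statement of which carries the conclusion. A pre-post change in the intervention arm is not a comparison with control: both arms wear the tracker, and the Discussion itself recognises reactivity to monitoring. In addition, because effect sizes are restricted to significant variables, the unadjusted threshold also decides which effects are given a Cohen d.

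**Working it through.** **1. The plan's own figure**

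Inputs from Sample Size Calculation: difference 3, SD 5, alpha .05, power .80. The test is taken as two-sided; this is stated only for the baseline comparison ("2-tailed Student" t test), not for the sizing.

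n per group = 2 × (1.960 + 0.842)² × SD² / difference²

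- Stated inputs: 2 × 7.849 × 25 / 9 = 43.6, so 44 per group (45 with the t distribution). The stated 99 is not reproduced.
- Difference 2, SD 5: 2 × 7.849 × 25 / 4 = 98.1, so 99.
- Difference 3, SD 7.5: 2 × 7.849 × 56.25 / 9 = 98.1, so 99.

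This mismatch is a separate matter. It is relevant here only to whether a single primary outcome would need more participants. With 99 per group and SD 5, the standard error is 5 × √(2/99) = 0.711. Power at two-sided .05 is then:

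- difference 3: Φ(3/0.711 − 1.96) = 98.8%
- difference 2: Φ(2/0.711 − 1.96) = about 80%

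**2. Number of outcomes (assumption)**

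The article gives no count. Reading the measurement sections gives 7: estimated maximum oxygen consumption, right grip, left grip, BMI, waist, adipose percentage and muscle percentage. The count would be 6 if the two hands were merged, 8 if weight were tested as well, and perhaps 14 or more if skinfolds, perimeters and diameters were each tested.

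**3. Chance of at least one false-positive between-group result**

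Independent outcomes, either direction: 1 − 0.95^k. Independent outcomes, favourable direction only: 1 − 0.975^k. The correlated columns assume jointly normal test statistics with every pairwise correlation 0.5, which is an illustrative value.

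| Outcomes k | Either direction, independent | Either direction, corr. 0.5 | Favourable, independent | Favourable, corr. 0.5 |
|---|---|---|---|---|
| 3 | 14.3% | 12.5% | 7.3% | 6.3% |
| 6 | 26.5% | 20.7% | 14.1% | 10.4% |
| 7 | 30.2% | 23.0% | 16.2% | 11.5% |
| 8 | 33.7% | 25.0% | 18.3% | 12.5% |
| 14 | 51.2% | 34.8% | 29.8% | 17.4% |

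The reference values for one two-sided test are 5% (either direction) and 2.5% (favourable). At still higher correlation the inflation shrinks: for k = 7 and correlation 0.9, simulation gives about 11% (either direction) and 6% (favourable).

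**4. Adding the within-group tests**

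Simulation with k = 7, an assumed pre-post correlation of 0.8 and no true change in either arm:

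- favourable between-group result or favourable change within the intervention arm: 21% (correlation 0.5) to 29% (independent)
- any significant result among the between-group tests and both arms' within-group tests, either direction: about 54% to 65%

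The second line overstates the risk to the trial's conclusion, because a control-arm change cannot by itself support a claim for the intervention.

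**The case against.** **The ranking may exist elsewhere.** This is a condensed article. A registry record is cited but not at hand, and a fuller protocol or analysis plan may rank outcomes or handle multiplicity. That limits the point to what the article states. It does not remove it: the article is not silent, since it sets an unadjusted threshold for all tests, and a later plan that ranked or adjusted outcomes would have to depart from that sentence.

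**Cardiorespiratory fitness is implicitly the lead outcome.** It is the only sizing variable and comes first in the lists of outcomes. That is a fair reading, but nothing in the analysis section gives it that role.

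**The outcome count is uncertain.** This stands. The two grip values are one construct, the body-composition measures overlap, and the article does not say that each skinfold or diameter is tested. The figures are therefore a range under stated assumptions.

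**Two stronger readings are not supported.**

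- A reader might infer that a spurious improved indicator is likely. With 7 or 8 between-group tests, the chance of any false positive is 23% to 34%, and of a favourable one 11.5% to 18%. It passes 50% only by counting control-arm or unfavourable results, or about 14 independent outcomes.
- A reader might infer a rule that any single significant indicator proves benefit. The wording about some indicators is Introduction rationale, and the analysis section gives a per-test threshold, not a success criterion. What the article lacks is a statement of which result carries the conclusion.

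**Conclusion.** The concern holds in a limited form. The article fixes P<.05 for every test and names no primary outcome, while sizing the trial at alpha .05 on one domain only. For about 7 analysed outcomes, the chance of at least one false-positive between-group result is about 23% to 30% instead of 5%, and of a falsely favourable one about 11.5% to 16% instead of 2.5%. These figures rest on the assumed count of 7, correlations between 0 and 0.5, and no true effect on any outcome. Within-group tests raise the chance further and do not test the intervention against control.

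The data would remain usable. What lacks its stated error control is a headline claim selected from the full set of tests. Whether the registry already names a primary outcome could not be checked.

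**What to change.** 1. **Reconcile the sizing variable with the measure.** Sample Size Calculation uses a percentage scale for endurance, whereas the Cardiorespiratory Fitness section records the shuttle-run minute reached and estimates maximum oxygen consumption from it. State which variable and unit the difference and SD refer to.
2. **Name one primary outcome and contrast:** the between-group difference in cardiorespiratory fitness from the 20-m shuttle run at final evaluation, tested at two-sided .05. If the registry already names a primary outcome, the article must agree with it.
3. **Base the conclusion on that contrast.** Treat all other outcomes and all within-group tests as secondary or exploratory. Either adjust them for multiplicity (Holm's method is one option; the choice is not essential) or report estimates with confidence intervals and make no confirmatory claim.

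Settle this before any between-group outcome data are seen.

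**Cost.** Wording in the protocol and, if needed, the registry. Secondary findings can no longer carry the headline claim. No participants are added: at 99 per group, a single primary test has 98.8% power for the stated difference of 3 (SD 5) and about 80% for a difference of 2. Keeping 7 co-equal outcomes under Bonferroni (.05/7 = .0071) would instead give 93.7% and 54.9%.
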